### JTHFT

The JTHFT is a timed, 7-subtest assessment designed to evaluate hand functionality. The test is derived from common daily activities and includes the following tasks: writing a standardized 24-letter sentence, turning 5 cards, picking up small objects, picking up 5 beans using a spoon, stacking 4 checkers on a test board, moving 5 large empty cans, and moving 5 full cans. Since the study population includes children who may not yet be literate according to the age criteria, the first subtest (writing a sentence) will be omitted from the evaluation. Each subtest allows a maximum of 120 seconds for successful completion. All subtests are first performed with the nondominant hand, followed by the dominant hand. The validity and reliability of the JTHFT in children with CP aged 6‐18 years have been established by Tofani et al [34].

### Selective Control of the Upper Extremity Scale

The Selective Control of the Upper Extremity Scale (SCUES) was developed to assess selective voluntary motor control (SVMC) of the upper extremity and represents the first scale specifically designed for this purpose. It is a practical and user-friendly, video-based assessment tool that can be administered in less than 15 minutes. During the evaluation, the physiotherapist first demonstrates the required joint motion passively within the desired ROM and then asks the child to perform the movement 3 times at each joint. The test provides the opportunity to assess selective movements in all upper extremity joints, including the shoulder, elbow, forearm, wrist, and fingers. Each of the 5 joint regions is scored on a 4-point ordinal scale: absence of SVMC (0 points), moderately reduced SVMC (1 point), mildly reduced SVMC (2 points), and normal SVMC (3 points). The total SCUES score ranges from 0 to 15, with higher scores indicating better SVMC [35]. In the present study, only the selective control of the upper extremities will be assessed bilaterally.

### sEMG

sEMG is based on the principle that there is a linear relationship between sEMG signal amplitude and muscle contraction force, with signal amplitude increasing as muscle force increases [36]. sEMG can be used as an outcome measure in children with CP, providing quantitative information related to motor activation when the processes are correctly analyzed [37]. In the present study, muscle activation will be assessed using the Natus UltraPro S100 (Electromyography (EMG)/Nerve Conduction Studies (NCS)/Evoked Potentials (EP) neurodiagnostic system; Natus Medical Incorporated). Surface electrodes will be applied to measure muscle activity. The child will be asked to perform maximum voluntary contraction, and the sEMG signals from the muscles will be recorded for 10‐15 seconds, followed by a 10-second rest period (Figure 2) [38]. Electrodes will be positioned parallel to the muscle fibers over the wrist extensor and flexor muscle bellies Figure 3A using anatomical landmarks in accordance with the guidelines of the Surface Electromyography for the Noninvasive Assessment of Muscles (SENIAM) [39]. To ensure consistency across assessment time points, electrode placement will be performed by the same neurology specialist.

**Figure 2. F2:**
[figure not shown]
Screenshot of the surface electromyography (sEMG) recording interface.

The sEMG signal processing procedure will be performed as follows: raw sEMG signals will be processed using a 20 Hz infinite impulse response Butterworth high-pass filter and then a 500 Hz infinite impulse response Butterworth low-pass filter will be applied to reduce movement artifacts and high-frequency noise. Subsequently, root mean square values will be derived from the filtered sEMG signals using consecutive 0.1-second time windows for signal analysis. The filtered sEMG signals will then be analyzed using root mean square amplitude values expressed in microvolts (µV), without additional normalization to maximum voluntary contraction. Each measurement will be repeated 3 times, and activation of the wrist extensor and flexor muscles will be recorded (Figure 3B). To minimize signal variability in the pediatric population, standardized verbal instructions will be provided, measurements will be repeated with rest intervals, recordings with visible movement artifacts will be excluded, and the mean value of valid trials will be used for analysis.

**Figure 3. F3:**
[figure not shown]
Surface electromyography (sEMG): (A) electrode placement over the wrist extensor and wrist flexor muscle groups; (B) testing procedure.

### Goniometric Assessment

Active wrist ROM will be assessed with Joints Digital Goniometer 360 ^0^ (JTECH Medical) [40]. In addition to digital goniometer measurements, wrist ROM will be assessed with a Becure HandROM (Becure GmbH) application integrated into the LMC. Wrist flexion, extension, ulnar deviation, and radial deviation ROM will be measured bilaterally. Each measurement will be repeated 3 times, and the mean value will be used for statistical analysis.

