**Methods:**

This study is a 2-arm, parallel-group randomized controlled trial with a 1:1 allocation ratio and will include 30 children aged 6‐15 years with spastic CP and distal upper extremity involvement. All participants meeting the inclusion criteria will undergo baseline assessments at T0, where wrist range of motion will be measured using an electronic goniometer; selective motor control will be evaluated using the Selective Control of the Upper Extremity Scale (SCUES); hand function will be assessed using the Jebsen-Taylor Hand Function Test; daily hand use will be evaluated using the ABILHAND-Kids questionnaire; and wrist extensor and flexor muscle activation will be assessed using surface electromyography (sEMG). All participants will then undergo a 4-week conventional exercise program (3 sessions per week, 40 minutes per session). At the end of the 4 weeks, all baseline measurements will be repeated (T1). Subsequently, participants will be randomly assigned into 2 groups: the Leap Motion group (n=15) and the NMES group (n=15). Both groups will participate in an 8-week exercise program consisting of 3 sessions per week, 60 minutes per session (including 20 minutes of either Leap Motion–based exercise or NMES application, followed by 40 minutes of conventional exercise). At the end of this 8-week program, all assessments will be repeated (T2).

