### Randomization and Allocation

Patients who meet the inclusion criteria and agree to participate will be randomly assigned to one of 2 groups using a computer-based randomization program [28]. Block randomization will be applied to ensure balanced group sizes, with 15 participants allocated to each group (n=15). The random allocation sequence will be generated by an independent researcher who is not involved in participant enrollment, assessment, or intervention delivery. Allocation concealment will be ensured using sequentially numbered, opaque, sealed envelopes prepared prior to the 8-week intervention. Investigators responsible for participant recruitment and outcome assessment will not have access to the randomization sequence. Due to the nature of the interventions, blinding of participants and the treating physiotherapist will not be feasible. However, outcome assessments and statistical analyses will be conducted by assessors who are blinded to group allocation.

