### ABILHAND-Kids

The ABILHAND-Kids questionnaire will be used to assess hand use in daily life activities. ABILHAND-Kids is designed to measure upper extremity function in children with CP aged 6‐15 years and to evaluate unimanual and bimanual activities of the upper limbs as comprehensively as possible [41]. The questionnaire consists of 21 items covering both unimanual and bimanual tasks and will be completed by parents using a 3-point scale: 0-cannot perform the activity, 1-performs the activity with difficulty, and 2-performs the activity easily. The 21 items include daily tasks such as fastening pants buttons, fastening shirt buttons, opening a jar, zipping a jacket, sharpening a pencil, putting on a backpack, zipping pants, rolling up a sweater sleeve, applying toothpaste to a toothbrush, opening a bottle cap, opening a chip bag, opening a toothpaste tube, washing the upper body, filling a glass with water, opening a bread box, taking off a T-shirt, wearing a hat, retrieving coins from a pocket, opening a chocolate wrapper, turning on a bedside lamp, and opening jacket snaps. ABILHAND-Kids is a test specifically developed for children with CP and requires no preparatory phase. The Turkish validity and reliability study in children with CP was conducted by Sahin et al [42].

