### Leap Motion–Based Exercise Group

The Leap Motion–based VR system consists of a personal computer and an LMC, which are connected via a USB. Using infrared technology, the Leap Motion device allows for the tracking of multiple hand and finger movements without the need for markers or data gloves [20]. The Fizyosoft Becure company has developed software integrated into the Leap Motion system, creating task-oriented games designed to improve grasping ability and hand activities in individuals with upper extremity limitations. These games represent the first Turkish-language software developed for the Leap Motion system [45]. Each session of the VR intervention will last for 20 minutes and will use games developed within the Becure HandROM platform.

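### Wrist ROM is measured partly on the HandROM platform that only the Leap Motion arm trains on; the goniometer should be named as the sole between-arm ROM outcome

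*Protocol article*

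**What the plan says.** The Goniometric Assessment section of the protocol article describes two instruments for wrist ROM. The first is a digital goniometer: "Active wrist ROM will be assessed with Joints Digital Goniometer 360". The second comes on top of it: "wrist ROM will be assessed with a Becure HandROM (Becure GmbH) application integrated into the LMC". Flexion, extension, ulnar deviation and radial deviation are measured on both sides. The section closes with "Each measurement will be repeated 3 times, and the mean value will be used for statistical analysis" and does not say from which instrument. The abstract gives one instrument only: "wrist range of motion will be measured using an electronic goniometer".

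The Leap Motion–Based Exercise Group section describes the training: "Each session of the VR intervention will last for 20 minutes and will use games developed within the Becure HandROM platform". The text under Pong adds that these children are shown how to position themselves relative to the sensor and may practise before training starts. The NMES Training Protocol section lists NMES and conventional exercise, with no use of the Leap Motion Controller.

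Under Outcome Measures, wrist ROM and daily hand use are secondary outcomes, and the main comparison is the T1 to T2 change between groups. Under Participants, secondary outcomes are called exploratory.

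On blinding, Randomization and Allocation says that participants and the treating physiotherapist cannot be blinded, but that "outcome assessments and statistical analyses will be conducted by assessors who are blinded to group allocation". No outcome is excepted. ABILHAND-Kids "will be completed by parents using a 3-point scale".

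**The concern.** One of the two ROM instruments belongs to the treatment of one arm. Between T1 and T2, Leap Motion children repeatedly move the wrist over that sensor, inside that software platform, after being taught where to hold the hand. NMES children do not. If familiarity with the sensor helps a child to produce or hold a larger recorded range, a HandROM difference at T2 mixes a change in the wrist with a change in how well the child uses the device. The difference in exposure arises after randomisation, so randomisation does not balance it. It acts through the child's performance, so a blinded assessor does not remove it.

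The goniometer is free of this problem. What makes it a matter for the protocol is that the article does not settle which of the two readings is tested between arms.

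A smaller point concerns ABILHAND-Kids. A statement that outcome assessment is done by blinded assessors cannot cover a questionnaire whose rater is the parent.

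**Working it through.** No figure stated in the protocol depends on this point, so there is none to reproduce. The check compares exposure to the measuring platform by arm and counts the affected results.

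**Exposure between T1 and T2.** Inputs: 3 sessions per week for 8 weeks (abstract, Methods) and 20 minutes per session on the platform (Leap Motion–Based Exercise Group).
- Leap Motion arm: 3 × 8 = 24 sessions; 24 × 20 = 480 minutes planned.
- NMES arm: 0 minutes of training on the platform.

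**Exposure before randomisation, both arms.** Inputs: 4 movements, 2 sides, 3 repeats (Goniometric Assessment), taking HandROM to be among the measurements made at T0 and repeated at T1.
- Per visit: 4 × 2 × 3 = 24 HandROM trials.
- T0 and T1 together: 2 × 24 = 48 trials for every child.

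The instrument is therefore new to neither arm at T2. The arms differ in what happens after T1.

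**Number of ROM results.**
- 4 movements × 2 sides × 2 instruments = 16, of which 8 are on HandROM.
- bRabbit and Pong are described as repetitive wrist flexion and extension. Leap Ball uses finger flexors, then finger and wrist extensors. No game is described as training radial or ulnar deviation.
- Practice of the measured movement itself therefore reaches 2 movements × 2 sides = 4 of the 8 HandROM results. Only the weaker argument, familiarity with the sensor and its positioning, reaches the other 4.

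**What a familiarity effect would do, as an illustration only.** The protocol gives no size for such an effect. Assume that familiarity alone shifts the HandROM reading in the Leap Motion arm by d standard deviations, with no true ROM difference, and that the arms are compared with a two-sided 5% t test. With n per arm, the noncentrality is d × √(n/2) on 2n − 2 degrees of freedom. The chance of a significant result, which would be 5% at d = 0, is:

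| Assumed shift d (SD) | 15 per arm | 12 per arm |
|---|---|---|
| 0.25 | 10% | 9% |
| 0.50 | 26% | 22% |
| 0.75 | 51% | 42% |
| 1.00 | 75% | 65% |

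Here 15 is the planned group size and 12 is half the stated minimum of 24. The shifts are assumptions chosen to show a range. The table does not estimate what will happen in this trial.

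**Which reading is analysed.** The abstract lists the goniometer alone. The Goniometric Assessment section lists the goniometer and then HandROM, and sends a mean value to analysis without attaching it to either.

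**Blinding.** Randomization and Allocation describes blinded assessors without exception, while the ABILHAND-Kids section names parents as the raters. That parents know the allocation is an inference: they consent for the child, the child is unblinded, and electrical stimulation and computer games are plainly different. The limitations in the Discussion mention performance bias and motivational bias, but neither the shared platform nor the parent rating.

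**The case against.** The strongest reply is that the goniometer is already the main instrument. It gives the section its heading, it is named first, HandROM is introduced as an addition, and the abstract mentions nothing else. That is a natural reading and it supports the fix. It does not close the point, because the sentence that sends a mean to analysis follows both instruments and distinguishes neither.

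Second, a learning effect is not demonstrated. Every child meets HandROM before randomisation, the Introduction reports the controller to be highly accurate for the four movements measured, and a gain in flexion or extension could be a genuine treatment effect. All of this stands, and it limits the claim to something that could contribute. Accuracy in tracking the hand does not, however, make performance equal between children with and without weeks of practice on the sensor. The goniometer reading helps to tell the two explanations apart, which is a reason to rest the comparison on it.

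Third, the consequence is limited. Both outcomes are secondary and exploratory, and the primary Jebsen-Taylor test is not measured on the device. This stands in full.

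A reader might infer more than the documents support:
- That any HandROM difference would be an artefact. Neither its presence nor its size is shown.
- That the more favourable of two readings will be reported. Nothing in the article suggests this.
- That a child's ease with the sensor will unblind the assessor. This is speculation.
- That the protocol denies expectation bias in ABILHAND-Kids. It does not: it states openly that parents complete the form and that participants are unblinded. The blinding sentence merely lacks an exception.

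**Conclusion.** The point holds in a limited form. One arm has 480 planned minutes on the platform that supplies the second ROM measurement, and the other has none, all within the window of the main comparison. A between-arm test of HandROM at T2 could therefore partly reflect device familiarity, most plausibly for flexion and extension. The size cannot be obtained from the protocol. That the direction favours Leap Motion, the arm hypothesised to do better, is likely but not established; it assumes that practice raises the recorded range. Because the analysed instrument is left open and a neutral one is already in use, the protocol should settle the choice. The primary outcome and the sample size are unaffected.

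The ABILHAND-Kids point is a minor correction of wording. It rests on the inference that parents very probably know the allocation.

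**What to change.** In Goniometric Assessment, name the digital goniometer as the only wrist ROM outcome for the between-arm comparison, in line with the abstract. State that HandROM values will be reported descriptively by arm and visit, without a between-arm test, because one arm trains on that platform. Visit procedures stay as they are.

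In Randomization and Allocation, limit the blinded-assessment statement to tests administered by an assessor. Describe ABILHAND-Kids as an unblinded parent report when it is interpreted, and add the shared platform and the parent rating to the limitations.

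The cost is a change of wording and the loss of between-arm inference on HandROM. No new measurement is needed. The Results section reports 11 participants enrolled as of June 2026, with analysis to follow once all have completed, so the choice can still be fixed before the data are analysed.

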### ABILHAND-Kids

The ABILHAND-Kids questionnaire will be used to assess hand use in daily life activities. ABILHAND-Kids is designed to measure upper extremity function in children with CP aged 6‐15 years and to evaluate unimanual and bimanual activities of the upper limbs as comprehensively as possible [41]. The questionnaire consists of 21 items covering both unimanual and bimanual tasks and will be completed by parents using a 3-point scale: 0-cannot perform the activity, 1-performs the activity with difficulty, and 2-performs the activity easily. The 21 items include daily tasks such as fastening pants buttons, fastening shirt buttons, opening a jar, zipping a jacket, sharpening a pencil, putting on a backpack, zipping pants, rolling up a sweater sleeve, applying toothpaste to a toothbrush, opening a bottle cap, opening a chip bag, opening a toothpaste tube, washing the upper body, filling a glass with water, opening a bread box, taking off a T-shirt, wearing a hat, retrieving coins from a pocket, opening a chocolate wrapper, turning on a bedside lamp, and opening jacket snaps. ABILHAND-Kids is a test specifically developed for children with CP and requires no preparatory phase. The Turkish validity and reliability study in children with CP was conducted by Sahin et al [42].

### Interventions

This study consists of 5 sequential phases. In the first phase, eligibility of the participants will be assessed according to the predefined inclusion criteria and written informed consent will be obtained. In the second phase, baseline assessments will be conducted (T0). In the third phase, all participants will undergo a 4-week conventional exercise program before randomization, followed by midintervention assessments (T1). In the fourth phase, participants will be randomized into either the Leap Motion–based exercise group or the NMES group, and both groups will receive these interventions in addition to conventional exercise for 8 weeks. In the fifth and final phase, all outcome measures will be reassessed after completion of the intervention period, and the study will be closed out (T2).

Treatment adherence will be monitored using standardized follow-up forms, including session attendance, completed sessions, missed sessions, and adherence to the intervention protocol. All interventions in the NMES and Leap Motion–based training groups as well as the conventional exercise program will be conducted by the same pediatric physiotherapist with at least 8 years of experience. In addition, external rehabilitation programs will be discontinued after enrollment in this study.

### Conventional Exercise Program

All participants who meet the inclusion criteria and provide informed consent will be enrolled in a 4-week conventional exercise program. The conventional exercise program will be administered 3 times per week, with each session lasting 40 minutes. The program will be structured at the beginning of the treatment period by selecting exercises from a predefined pool of neurodevelopmental treatment–based upper extremity exercises, including bilateral and unilateral upper extremity weight-bearing activities for tone regulation, passive stretching, muscle strengthening, and active ROM exercises. To improve fine motor skills, activities targeting reaching, grasping, releasing, carrying, in-hand manipulation skills, and bimanual use will also be included. The exercises will be selected and incorporated into the program based on each child’s level of impairment and clinical needs. After randomization, the selected exercises will be applied consistently across sessions for 8 weeks in addition to the group-specific interventions. While the session duration and frequency will remain standardized, exercise intensity will be adjusted by modifying the number of repetitions according to the child’s tolerance and performance.

### NMES Group

For NMES application, a portable 4-channel device (Globus Premium-400; Globus Corporation Srl) will be used. The NMES provides a biphasic waveform, with a pulse duration ranging between 50 and 300 μs and a frequency range of 1‐120 Hz. In spastic CP, stimulation frequencies between 10 and 60 Hz are generally recommended to elicit motor activation, although frequencies above 50 Hz may induce muscle fatigue [43]. In this study, stimulation parameters will be set to a pulse duration of 300 μs, a frequency of 30 Hz, and an on/off ratio of 10 s/10 s [44]. The stimulation intensity will be increased until visible muscle contraction is observed and will then be adjusted to the maximum level tolerated by the participant. The intervention will be administered for 20 minutes per session, in addition to the conventional exercise program, over a period of 8 weeks. Electrode placement will be as follows: the inactive electrode on the dorsal aspect of the wrist, and the active electrode on the lateral forearm over the bellies of wrist extensor muscles (extensor carpi radialis longus and brevis, extensor carpi ulnaris). For participants with bilateral spastic CP, stimulation will be applied to the dominant side, whereas for those with unilateral spastic CP, it will be applied to the affected side. During the first 2 weeks, NMES will be applied passively (Figure 4A). In subsequent sessions, active participation will be encouraged by asking participants to perform wrist extension synchronously with the stimulation (Figures 4B and 4C). During the sessions, children will be monitored for pain, discomfort, muscle fatigue, skin irritation, redness at the electrode site, or any adverse response. Any adverse events will be recorded, and the session will be stopped if necessary.

